## Abstract

**Background:**

Integrating information on bodily functions, pain intensity and quality of life into one composite measure of a holistic responder has recently been proposed as a useful method to evaluate treatment efficacy of spinal cord stimulation (SCS) in patients with therapy-refractory persistent spinal pain syndrome type II (PSPS-T2). Previous studies already demonstrated the efficacy of standard SCS over best medical treatment (BMT) and the superiority of new subthreshold (i.e. paresthesia free) SCS paradigms compared to standard SCS. Nevertheless, the efficacy of subthreshold SCS compared to BMT has not yet been investigated in patients with PSPS-T2, neither with unidimensional outcomes nor with a composite measure. The current objective is to examine whether subthreshold SCS, compared to BMT, provided to patients with PSPS-T2 results in a different proportion of clinical holistic responders (as composite measure) at 6 months.

**Methods:**

A two-arm multicentre randomised controlled trial will be conducted whereby 114 patients will be randomised (1:1) to (a) BMT or (b) paresthesia-free SCS. After a follow-up period of 6 months (primary time endpoint), patients receive the opportunity to cross over towards the other treatment group. The primary outcome is the proportion of clinical holistic responders at 6 months (i.e. a composite measure of pain intensity, medication, disability, health-related quality of life and patient satisfaction). The secondary outcomes are work status, self-management, anxiety, depression and healthcare expenditure.

**Discussion:**

Within the TRADITION project, we propose to shift the focus from a unidimensional outcome measure towards a composite measure as primary outcome measure to evaluate the efficacy of currently used subthreshold SCS paradigms. The lack of methodologically rigorous trials exploring the clinical efficacy and socio-economic consequences of subthreshold SCS paradigms is pressing, especially in light of the growing burden of PSPS-T2 on the society.

**Trial registration:**

ClinicalTrials.gov NCT05169047. Registered on December 23, 2021

## Administrative information

Note: the numbers in curly brackets in this protocol refer to SPIRIT checklist item numbers. The order of the items has been modified to group similar items (see http://www.equator-network.org/reporting-guidelines/spirit-2013-statement-defining-standard-protocol-items-for-clinical-trials/).

## Introduction

### Background and rationale {6a}

Patients suffering from persistent or recurring low back pain despite having undergone lumbosacral spine surgery, sometimes associated with referred or radiating leg pain [1], are denoted as suffering from chronic pain after spinal surgery or persistent spinal pain syndrome type 2 (PSPS-T2) [2]. This heterogeneous group of patients with PSPS-T2, based on aetiology and multilevel complaints (e.g. pain intensity, limited functionality), ends up with chronic pain and disability, which severely impacts individual’s health-related quality of life and patient participation, has a high psychological morbidity and poses a high socio-economic burden to society [3, 4].

Treatment of PSPS-T2 is complex as the condition involves neuropathic and/or nociceptive elements [5], whereby spinal cord stimulation (SCS) may serve as preferred option in case conservative treatment is not successful [6]. SCS is a type of neuromodulation that involves the implantation of an epidural electrode, connected through extensions with a subcutaneous implanted pulse generator [7]. Electrical pulses at different frequencies are generated and delivered to the spinal cord to elicit paresthesia in the painful area [8]. The efficacy of SCS in patients with PSPS-T2 has been demonstrated in several randomised controlled trials, clearly pointing out the value of SCS in comparison to conventional management. In the PROCESS trial [9], 100 patients with PSPS-T2 were randomised to either SCS with best medical treatment (BMT) or BMT alone. The primary outcome, i.e. the proportion of patients achieving 50% or more pain relief in the legs at 6 months, was obtained by 48% and 9% in the SCS + BMT and BMT, respectively [10]. In 2019, the PROMISE trial was published in which 218 PSPS-T2 patients with predominant low back pain were randomised to SCS + BMT versus BMT. In this trial, the primary outcome, i.e. the proportion of patients achieving ≥ 50% pain relief in the back at 6 months, was obtained by 13.6% and 4.6% in the SCS + BMT and BMT, respectively [11].

Since its first application in 1967, different stimulation parameters have been investigated to optimise the therapeutic efficacy of SCS [12]. The initial success of SCS was based on obtaining an adequate coverage over the patients’ pain areas with paresthesia by manipulating the pulse width or amplitude in a therapeutic way [13]. However, this traditional manner of stimulation has important limitations, as not every patient tolerates the sensation of paresthesias, leading to failure of SCS [14, 15]. In the last decade, the focus shifted towards the application of paresthesia-free paradigms, whereby superiority of the newer SCS designs was claimed in comparison to standard SCS [16, 17]. Nevertheless, all these studies explored a new subthreshold SCS paradigm compared to standard SCS, thereby relying on previous literature that standard SCS is better than BMT to obtain pain relief, and consequently fall back upon an indirect comparison. Up till now, there is no direct head-to-head evidence that new subthreshold SCS stimulation paradigms, i.e. those that are not providing paresthesia, are better than BMT for patients with PSPS-T2. Moreover, the primary outcome measurement of all previously mentioned trials was to obtain a pain intensity reduction, which entails a unidimensional primary outcome measure. This is in strong contrast with the recently proposed initiatives to shift towards a more comprehensive outcome measure, i.e. evaluating patients from a holistic point of view, taking functioning, medication use, quality of life, satisfaction and other measures into account besides pain intensity scores [18–23]. It thus becomes clear that only focusing on a pain intensity reporting is a serious denial of the complexity of pain [24].

### Objectives {7}

Given the substantial socioeconomic impact of SCS implantations, given that currently no direct high-quality evidence is available for subthreshold SCS versus BMT and given the lack of a holistic outcome to guide the treatment choice between subthreshold SCS versus BMT in patients with PSPS-T2, we here propose a randomised controlled trial to answer this question.

The primary scientific objective is to examine whether subthreshold SCS, compared to BMT, provided to patients with PSPS-T2 results in a different proportion of clinical holistic responders at 6 months. The secondary objective of the study is to examine if subthreshold SCS compared with BMT is different in improving patients’ individual competencies for self-management, increasing the likelihood to return to work, work status and healthcare expenditure, improving pain relief, obtaining pain medication reduction, decreasing anxiety and depression, increasing quality of life and decreasing disability.

### Trial design {8}

TRADITION is a two-arm, cross-over multicentre randomised controlled trial to evaluate whether subthreshold SCS results in more clinical holistic responders in PSPS-T2 patients compared with BMT. This research is a post-market clinical follow-up (PMCF) investigation [25]. Patients will be randomised (1:1) to (a) BMT or (b) subthreshold SCS. After the assessment at 6 months, patients are allowed to switch groups in case of unsatisfactory responses. Patients will have a follow-up period until 12 months after the start of the intervention.

## Methods: participants, interventions and outcomes

### Study setting {9}

The study will be conducted in one academic hospital (Universitair Ziekenhuis Brussel) and four regional (non-academic) hospitals (AZ Turnhout, AZ Delta, Jessa Ziekenhuis and AZ Sint-Maarten). All study sites are located in Belgium. Details on study sites can be found at ClinicalTrials.gov with Identifier: NCT05169047 registered on December 23, 2021.

## Participants

### Eligibility criteria {10}

This study will focus on patients with PSPS-T2, defined as patients suffering from neuropathic pain of radicular origin with pain in the lower back and/or leg(s), of an intensity of at least 4/10 on the numeric rating scale, for a period of at least 6 months after a minimum of one anatomically successful spinal surgery and refractory to conservative treatment (according to Belgian reimbursement rules from January 1, 2018). All patients need to be eligible for subthreshold SCS implantation to be eligible for participation in the study. Patients need to be at least 18 years old.

Exclusion criteria are an expected inability to operate the SCS system, an existing pregnancy, evidence of an active psychiatric disorder, or suffering from another chronic illness characterised by chronic generalised widespread pain (e.g. rheumatoid arthritis, fibromyalgia, chronic fatigue syndrome, scleroderma).

### Who will take informed consent? {26a}

The treating neurosurgeon or anaesthesiologist (local principal investigator or his/her designee) will inform eligible patients about the project. Thereafter, an investigator of TRADITION will contact the patients by telephone to further inform eligible patients about the project. In case they provide oral consent, they will be screened for in- and exclusion criteria as listed above during this telephone call. Patients who are eligible for participation (based on the telephone interview) and are willing to participate will receive detailed oral and written information about the study and have the opportunity to ask questions. Subsequently, they will be asked to provide written informed consent before participation.

### Additional consent provisions for collection and use of participant data and biological specimens {26b}

No biological samples will be obtained throughout this study. There are no planned ancillary studies involving the collection or derivation of data for purposes that are separate from the main trial.

## Interventions

### Explanation for the choice of comparators {6b}

In clinical practice, the number of physicians that is still programming their patients on standard SCS is rather limited. Similarly, analysis of patients’ preferences revealed a clear trend toward paresthesia-free SCS [26]. Based on qualitative research in patients with PSPS-T2 towards goal identification with SCS, it became clear that besides pain relief, patients aimed to improve walking (100%), sitting (73%), driving a car (67%), feeling happy (73%) and regaining a social life (73%) which emphasises the importance of broad outcome measurements in chronic pain management [27, 28] and consequently a suitable composite measure.

### Intervention description {11a}

#### Control intervention: best medical treatment (BMT)

For each patient who is randomised to BMT, an optimal individual treatment plan will be developed by the treating physician. BMT can include oral medications (i.e. opioid, non-steroidal anti-inflammatory drug, antidepressant, anticonvulsant/antiepileptic and other analgesic therapies), nerve blocks, epidural adhesiolysis, neurotomies, physical and psychological rehabilitative therapy and/or chiropractic care [10, 11]. The protocol specifically excludes other invasive therapy, such as spinal surgery or implantation of an intrathecal drug delivery system. Starting from randomisation, BMT is actively managed and according to local clinical practice, where the treatment plan is optimised at each visit. The number of visits is according to standard clinical practice of the participating centres for PSPS-T2 patients. All interventions are documented in diaries for healthcare utilisation by the patients.

#### Experimental intervention: subthreshold SCS

Participants randomly allocated to subthreshold SCS will undergo two surgical interventions to implant the neurostimulator. According to the Belgian reimbursement rules, all patients first need a SCS-trial period of 3 weeks with an external neurostimulator. After a successful trial according to Belgian legislation, i.e. pain reduction of at least 50% and reduction in medication use of at least 50%, the external neurostimulator will be replaced by an internal pulse generator (IPG). The implanting physician is free to choose the type of IPG that will be implanted.

SCS will be programmed at subthreshold stimulation, next to the conventional medical treatment that each patient will receive. As such, this intervention is similar to the BMT group with the addition of subthreshold SCS. Several subthreshold SCS stimulation types are provided such as high frequency SCS, burst SCS, high-dose SCS and differential target multiplexed SCS. For all stimulation types, patients do no longer feel paresthesia. Programming to subthreshold SCS will be performed on the day of IPG implantation.

#### Criteria for discontinuing or modifying allocated interventions {11b}

The participants can withdraw from the study at any time. The intervention can be discontinued in case the treating physician considers this appropriate concerning patient safety.

#### Strategies to improve adherence to interventions {11c}

At the outcome assessments, patients will be asked to indicate what type of interventions they followed during the past period. No other formal verification will be performed to control adherence to BMT or SCS.

#### Relevant concomitant care permitted or prohibited during the trial {11d}

Patients randomised to BMT will be asked not to start the trial SCS procedure during the first 6 months. By imposing these restrictions, adherence to the protocol can be guaranteed, whereafter patients can cross-over to the other group.

#### Provisions for post-trial care {30}

This study does not provide post-trial care. There is no anticipated harm for trial participation and consequently no compensation for anticipated harm.

### Outcomes {12}

#### Primary outcome

The primary outcome measure is the proportion of clinical holistic responders at 6 months. This outcome measure consists of a combination of 5 questionnaires whereby all criteria need to be fulfilled to be considered a clinical holistic responder. For questionnaires where a minimal clinical important difference (MCID) is available, patients should reach this cut-off value. A patient is considered a responder if all of the following criteria are fulfilled:

30% VAS pain intensity reduction for overall pain compared to baseline [29]41% reduction in pain medication use compared to baseline [30]30% improvement on Oswestry disability index (ODI) compared to baseline [29]MCID on EuroQol (EQ-5D)-5L compared to baseline [31]Minimally improved, much improved or very much improved on Patient Global Impression of Change (PGIC) [32]

#### Secondary outcomes

The visual analogue scale (VAS; 100 mm) will be used for the assessment of overall pain, defined as a combination of back and leg pain (but not pain from other body parts). The VAS pain score is believed to be reliable, valid and sensitive to change [33, 34].

Medication use (type of medication, dosage and frequency) will be recorded at each visit. Medication will be converted to one score with the Medication Quantification Scale III (MQS). The MQS is designed to quantify pain medication regimens in a wide variety of pain conditions [35]. It provides a numerical output that represents the negative impact of each medication [36]. For each medication, a MQS score is calculated by multiplying a detriment weight for a given pharmacologic class with a score for dosage [37]. Medication is subdivided into five classes: non-steroidal anti-inflammatory drugs (NSAIDs), muscle relaxants, neuropathic pain medications (antidepressants and anticonvulsants), benzodiazepines and opioids. All calculated values are summed to obtain a total MQS score. The cut-off value of 41% reduction in pain medication is calculated in this population [30].

The Oswestry disability index (ODI) is used to measure functional disability due to abnormalities of the spine [38, 39]. It contains ten topics for which each topic is scored on a scale from zero (no disability) to five (maximum disability possible). A total score of 100% indicates total disability, and higher scores correspond to more disability.

Health-related quality of life is assessed by the EuroQol with five dimensions and 5 levels (EQ-5D-5L) [40]. Patients subjectively tick the box with the most appropriate statement in each of the 5 dimensions (mobility, self-care, usual activities, pain/discomfort and anxiety/depression). The EQ-5D-5L index scores range from − 0.42 to 1, with 0 and 1 corresponding respectively to death and full health, based on preference-weighted health state classification algorithms [41]. Belgian population norms are available for the EQ5D-5L [42].

Patients will be asked to quantify the impression of change after treatment using the Patient Global Impression of Change scale (PGIC). The PGIC consist of a seven-point Likert scale asking the respondent to rate the overall level of improvement since the start of the treatment as “very much improved”, “much improved”, “minimally improved”, “no change”, “minimally worse”, “much worse” and “very much worse”[43].

A self-constructed questionnaire from the public health department of the VUB, specifically developed for a previous study evaluating return to work after spine surgery [44, 45] will be used to evaluate the work status. At baseline, current work status, job type, job description and work regime (e.g. full-time, part-time) will be asked. At the follow-up visits, patients will need to fill in whether they already resumed professional activities and, if yes, since when and to what extent. Additionally, patients will receive the opportunity to indicate whether a job change was needed or whether their job content needed to be changed to enable effective work resumption.

Patient Activation Measure-13 (PAM) is a 13-item instrument which assesses self-reported behaviour, knowledge and confidence for self-management of one’s health. PAM- 13 has proven to be a reliable instrument to measure patient activation and self-management [46, 47]. Patients will be divided in 4 levels, going from disengaged with lack of confidence (level 1) to individuals who maintain their healthy lifestyle and feel confident about their health (level 4).

The hospital Anxiety and Depression Scale (HADS) aims to measure symptoms of anxiety and depression and consists of 14 items: seven items for the anxiety subscale (HADS Anxiety) and seven for the depression subscale (HADS Depression). Each item is scored on a response-scale with four alternatives ranging between 0 and 3. After adjusting for six items that are reversed scored, all responses are summed to obtain the two subscales. Recommended cut-off scores are 8–10 for doubtful cases and ≥ 11 for definite cases [48]. HADS was found to perform well in assessing the symptom severity of anxiety disorders and depression in both somatic, psychiatric and primary care patients and in the general population [49].

Health seeking behaviour will be evaluated by self-reporting methods (diaries and questionnaires) [44]. Hence, healthcare expenditure includes hospital stays and any kind of treatments and consultations (e.g. pain killers, physiotherapy, psychotherapy) multiplied by their respective unit costs, derived from National Tariffs lists.

At baseline, all outcome measurements will be evaluated except for the impression of change and healthcare expenditure. Follow-up assessments will be performed one month after the start of the individualized best conservative treatment (BMT group) or 1 month after IPG implantation (SCS group), 6 months after start of the intervention (intermediate effects and primary endpoint) and 12 months (long-term effects) after intervention initiation. At 1 month and 12 months, outcome measurements can be completed without an additional hospital visit. Patients will receive a link towards the questionnaires to complete them online. At the 6-month follow-up, patients will complete the questionnaires at the hospital. After filling in the questionnaires at the 6-month follow-up visit, patients could change treatment groups (in both directions). This decision will be a shared decision between the patient and treating physician in case the randomised intervention did not provided enough pain relief. The cross-over will be mainly performed from BMT towards subthreshold SCS, according to study results obtained by Kumar et al. who evaluated standard SCS compared to BMT [10]. Figure 1 presents the project flowchart.

**Fig. 1 Fig1:**
[figure not shown]
Project flowchart. Participant timeline. n, number

##### Participant timeline {13}

The participant timeline for TRADITION is presented in Fig. 2.

**Fig. 2 Fig2:**
[figure not shown]
Participant timeline (SPIRIT). EQ5D, EuroQol with five dimensions and 5 levels; HADS, Hospital Anxiety and Depression Scale; HE, healthcare expenditure; int, intervention; MQS III, Medication Quantification Scale Version III; ODI, Oswestry disability index; PAM, Patient Activation Measure-13; PGIC, Patient Global Impression of Change; post-int, post-intervention; SCS, spinal cord stimulation; VAS, visual analogue scale

#### Sample size {14}

Sample size calculation was performed using the formula for large sample tests for proportions [50] and more specifically to test for equality between the proportion of clinical holistic responders in both interventions. The estimated proportion of clinical holistic responders is estimated at 47.8% in the subthreshold SCS group [51] and assumed to be 12.6% in the BMT group. The latter is an assumption based on the mean of the difference in primary outcome measures from the PROCESS and PROMISE trials at 6 months since no values for clinical holistic responders in BMT are available yet [10, 11]. By assuming an equal allocation, a sample size of 114 participants is needed with 57 participants in each intervention group. This sample size calculation accounts for a 20% loss to follow-up after 6 months and a 12% trial failure rate [51]. Calculations were performed for achieving an 80% power at the 5% level of significance.

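### The stated 80% power does not produce 57 patients per arm: the stated inputs need 66 to 90 patients in total, and 114 gives roughly 90–97% power

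*Protocol article*

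**What the plan says.** All points are in the protocol article.

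- **Method** (Sample size {14}): "Sample size calculation was performed using the formula for large sample tests for proportions", and more specifically "to test for equality between the proportion of clinical holistic responders in both interventions".
- **Rates** (same section): "The estimated proportion of clinical holistic responders is estimated at 47.8% in the subthreshold SCS group". The BMT rate is set at 12.6%, described as "an assumption based on the mean of the difference in primary outcome measures from the PROCESS and PROMISE trials".
- **Error rates** (same section): "Calculations were performed for achieving an 80% power at the 5% level of significance".
- **Result** (same section): "By assuming an equal allocation, a sample size of 114 participants is needed with 57 participants in each intervention group". This is said to cover 20% loss to follow-up and a 12% trial failure rate.
- **Earlier trials** (Background and rationale {6a}): in PROCESS the primary outcome "was obtained by 48% and 9% in the SCS + BMT and BMT, respectively"; in PROMISE it "was obtained by 13.6% and 4.6% in the SCS + BMT and BMT, respectively".

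The section does not state the variance form, any continuity correction, the sidedness in words, or how the two allowances were combined.

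**The concern.** The section gives the rates, the level, the power, the allocation and both allowances, so the result can be recomputed. It comes out well below 114. This is a disagreement among stated figures, not detail left to a fuller document. If the power is misreported, anyone who later weighs a null or borderline primary result will use the wrong power. If the power is right, some other input must be misreported.

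The description of the control rate adds a smaller difficulty. A difference between two proportions is usually taken as absolute, and on that reading the text leads to a rate other than 12.6%. The protocol acknowledges that no BMT values exist for this composite, so a reader needs to be able to follow where the rate comes from.

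**Working it through.** **Inputs.** p1 = 0.478, p2 = 0.126, d = 0.352, 1:1 allocation. A test of equality is taken as two-sided: z = 1.960 for 5%, 0.8416 for 80% power, 1.2816 for 90%. The variance sum is 0.478×0.522 + 0.126×0.874 = 0.2495 + 0.1101 = 0.3596. The mean rate is 0.302, so the pooled term is 2×0.302×0.698 = 0.4216.

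**Step 1. Evaluable patients per arm at 80% power**

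- Unpooled: (1.960 + 0.8416)² × 0.3596 / 0.352² = 22.8, so 23.
- Pooled: (1.960×√0.4216 + 0.8416×√0.3596)² / 0.352² = 25.5, so 26.
- Continuity-corrected: (25.5/4) × [1 + √(1 + 4/(25.5×0.352))]² = 30.9, so 31.

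**Step 2. Inflation.** Retention after both allowances is 0.80 × 0.88 = 0.704.

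| Form | Evaluable per arm | Divided by 0.704 | Randomised per arm | Total |
|---|---|---|---|---|
| Unpooled | 23 | 32.7 | 33 | 66 |
| Pooled | 26 | 36.9 | 37 | 74 |
| Continuity-corrected | 31 | 44.03 | 45 | 90 |

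Adding the allowances instead (dividing by 0.68) gives 68, 78 and 92. A one-sided test would need fewer patients and widen the gap. Counting trial failures as SCS non-responders (0.478 × 0.88 = 42.1%) and inflating only for loss gives 80 to 106. None of these reaches 114.

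**Step 3. What does give 57 per arm?** At 90% power the pooled form gives 33.6. With continuity correction, (33.6/4) × [1 + √(1 + 4/(33.6×0.352))]² = 39.1, so 40. Then 40/0.704 = 56.8, so 57 per arm and 114 in total.

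**Step 4. Power of 114 patients at the stated rates.** Unpooled power is Φ(d/s1 − 1.960) and pooled power is Φ((d − 1.960×s0)/s1). Here s1 is the standard error under the two rates and s0 the one under a common rate.

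| Treatment of trial failure | Evaluable SCS / BMT | Rates | Power (pooled, unpooled) |
|---|---|---|---|
| Removed from both arms | 40 / 40 (57×0.704 = 40.1) | 47.8% vs 12.6% | 94%, 96% |
| Removed from SCS arm only | 40.1 / 45.6 (57×0.8 = 45.6) | 47.8% vs 12.6% | 96%, 97% |
| Kept as SCS non-responders | 45.6 / 45.6 | 42.1% vs 12.6% | 90%, 92% |

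For the first row, s1 = √(0.3596/40) = 0.0948 and s0 = √(0.4216/40) = 0.1027. This gives Φ(0.352/0.0948 − 1.960) = 0.96 and Φ((0.352 − 1.960×0.1027)/0.0948) = 0.94. Fisher's exact test with 40 per arm gives 92%.

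**Step 5. The 12.6%**

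- As a ratio: BMT/SCS is 9/48 = 0.1875 in PROCESS and 4.6/13.6 = 0.338 in PROMISE. The mean is 0.263, and 0.263 × 47.8% = 12.57%, which rounds to the stated 12.6%.
- As an absolute difference: (39.0 + 9.0)/2 = 24.0 points, and 47.8 − 24.0 = 23.8%.

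**The case against.** **The mismatch is harmless.** The trial enrols more patients than its stated inputs require, and nothing about its conduct has to change. That stands. It limits the point to a reporting correction, but the printed power is still not the power of this design.

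**The 90% route is only a numerical match.** That also stands. The section mentions neither 90% power nor a continuity correction, and the cited formula source is not available here. The sponsor has to look up what was done.

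**The power of 114 is not one number.** SCS trial failure can arise only in the SCS arm, because BMT patients are asked not to start the SCS trial in the first 6 months. An intention-to-treat analysis is also planned, and it would keep trial failures in. Removing them from both arms is therefore only one of three readings, which is why a range is given. The figures also describe the simple two-proportion test named for the sample size, whereas the planned analysis is a covariate-adjusted generalised estimating equation. Every reading still lies well above 80%.

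**A stronger reading: the control rate is wrong and the trial underpowered.** A reader who takes the difference as absolute might infer a BMT rate of 23.8%. With 40 evaluable per arm, power would then be only 61–64%. The document does not support this. It does not say that the difference is absolute or that it is subtracted from 47.8%, and its own figures reproduce 12.6% through the mean ratio. The 23.8% is never assumed anywhere. What remains is imprecise wording.

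**Conclusion.** The sample size statement is wrong as written: 80% power at the stated rates and allowances needs 66 to 90 patients (92 with additive inflation), not 114. The excess is 24 to 48 patients on the multiplicative inflation. Conversely, 114 patients give 94–96% power if trial failures leave both arms, 96–97% if they leave the SCS arm only, and about 90–92% if they count as SCS non-responders. This rests on a two-sided 5% test of two proportions and on the stated rates being true.

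The error is on the safe side, so this is a correction to the report and not a threat to the trial. The 12.6% reconciles with the earlier trials' figures, and no underpowering is shown. Only its description needs tightening.

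**What to change.** Keep 114 patients. After checking the sponsor's own calculation, restate in the sample size section:

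1. the power actually used (90%, if that is what the calculation shows);
2. the formula, with its variance form, any continuity correction and the sidedness;
3. how the 20% loss and 12% trial failure were combined, and whether trial failure was applied to both arms or to the SCS arm only.

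As a minor wording change, if the sponsor confirms the route, describe the 12.6% as the mean BMT-to-SCS response ratio of PROCESS and PROMISE (0.263) applied to 47.8%.

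The cost is a few sentences. Enrolment, conduct and analysis do not change.

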#### Methods in analysis to handle protocol non-adherence and any statistical methods to handle missing data {20c}

Both intention-to-treat as well as per protocol analyses will be conducted to determine whether both definitions of the population will point towards similar results, which could improve robustness of the results. At first, analysis will be performed on data as observed. Hence, intermittent missing is not expected to substantially bias the results. To address possible informative drop-outs, a sensitivity analysis will be performed using multiple imputation, including all available information on background characteristics and outcome. All analysis will be performed in SAS or R.

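### The sample size treats patients who fail the SCS trial as attrition, and no rule keeps them in the SCS arm at 6 months, so the primary comparison can be selected on early response in one arm only

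*Protocol article*

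**What the plan says.** - **Order of events.** Under the experimental intervention heading, patients already allocated to SCS first have a 3-week trial with an external stimulator. The IPG follows only if the trial shows "pain reduction of at least 50% and reduction in medication use of at least 50" per cent. BMT patients are asked not to start an SCS trial in the first 6 months (section 11d).
- **Endpoint.** A responder must meet all five criteria. Two of them are a 30% pain reduction and a 41% medication reduction (Primary outcome).
- **Sample size {14}.** The SCS rate: "The estimated proportion of clinical holistic responders is estimated at 47.8% in the subthreshold SCS group". The BMT rate is "assumed to be 12.6% in the BMT group". The total is 114, or 57 per arm. On attrition: "This sample size calculation accounts for a 20% loss to follow-up after 6 months and a 12% trial failure rate". On error rates: "Calculations were performed for achieving an 80% power at the 5% level of significance".
- **Visit timing.** The follow-up schedule, at the end of the outcomes section, reads "1 month after IPG implantation (SCS group), 6 months after start of the intervention". It does not say whether the intervention starts in the SCS arm with the trial lead or with the IPG.
- **Analysis {20c}.** "Both intention-to-treat as well as per protocol analyses will be conducted", without saying which is primary. "At first, analysis will be performed on data as observed". Multiple imputation is a sensitivity analysis for possibly informative drop-out.
- **Silence.** No section says whether trial failures stay in follow-up, how they count in the responder outcome, or that they are excluded.

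**The concern.** A trial failure happens after randomisation and is itself a poor early response. The filter uses two of the five responder components, at cut-offs stricter than the endpoint's own, and it acts in the SCS arm only. If failures provide no 6-month data, the SCS arm consists of patients already selected for success, while the BMT arm consists of everyone randomised to it. The resulting bias has a known direction, in favour of SCS.

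An allowance for trial failure makes sense only if failures do not contribute to the analysis. Under intention-to-treat they do contribute, as SCS patients with whatever status they have at 6 months. The sample size section and section 20c therefore describe two different comparisons.

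The planned safeguards do not settle this. Section 20c expects little bias from intermittent missing values, but trial failure is neither intermittent nor random. Multiple imputation would borrow mainly from successfully trialled SCS patients and so tend to impute failures too favourably. A per-protocol set, which the article does not define, may omit them too. Agreement between the two sets would then not show the robustness that section 20c hopes for.

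**Working it through.** **Inputs (Sample size {14}).** SCS 47.8%, BMT 12.6%, difference 35.2 points; 5% level, taken as two-sided; 80% power; 57 per arm; 20% loss; 12% trial failure.

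**1. The plan's own figure.** The large-sample formula with pooled variance is

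n = [1.96·√(2p̄(1−p̄)) + z_power·√(p₁(1−p₁)+p₂(1−p₂))]² / (p₁−p₂)², with p̄ = (0.478+0.126)/2 = 0.302.

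| Power | Variant | Evaluable n per arm | ÷0.80÷0.88 |
|---|---|---|---|
| 80% | pooled | (1.273+0.505)²/0.352² → 26 | 37 |
| 80% | continuity-corrected | 31 | 45 |
| 90% | pooled | 34 | 49 |
| 90% | continuity-corrected | 40 | 57 |

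The stated 57 is not reproduced at 80% power. It is matched at 90% with continuity correction and both allowances: 40/0.80/0.88 = 56.8, rounded up to 57. This is an inference, because the text says 80%. If it is right, the 12% was also taken off the BMT arm, where patients are asked not to start an SCS trial before 6 months.

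**2. Patients affected.** 0.12 × 57 = 6.8, about 7 SCS patients. With both allowances, 57 × 0.80 × 0.88 = 40 SCS patients remain.

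**3. Effect on the SCS rate, assuming that 47.8% refers to implanted patients.**
- Failures never respond: 0.88 × 47.8% = 42.1%. Difference from BMT 42.1 − 12.6 = 29.5 points.
- Failures respond at the BMT rate: 42.1% + 0.12 × 12.6% = 43.6%. Difference 31.0 points.
- Overstatement if failures are dropped: 35.2 − 29.5 = 5.7 points, or 35.2 − 31.0 = 4.2 points.

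**4. The other assumption.** If 47.8% already includes failures, no rate correction is needed. The 12% allowance then counts them twice: once as low responders within the rate and again as lost patients.

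**5. Power with failures kept.** With 20% loss only, 57 × 0.80 = 45.6, taken as 45 per arm. Power = Φ{[(p₁−p₂)√n − 1.96·√(2p̄(1−p̄))] / √(p₁(1−p₁)+p₂(1−p₂))}.
- SCS 42.1%: Φ[(1.977 − 1.235)/0.595] = 89%.
- SCS 43.6%: Φ[(2.078 − 1.246)/0.597] = 92%.
- Fisher's exact test gives 85% and 88%.

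The pooled formula at 80% power needs 35 and 32 evaluable patients per arm, that is 44 and 40 after 20% loss. Both lie below 57.

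**The case against.** A reader might infer that trial failures have no primary visit at all, and that the protocol therefore compares selected SCS patients with all BMT patients. The documents do not support that. Only the 1-month SCS visit is tied to the IPG. The primary visit runs from the start of the intervention, and a patient who enters the SCS trial can fairly be said to have started. Section 18a schedules 6 months for both groups without an IPG condition, and section 11b separates stopping treatment from leaving the study. No section excludes failures, and intention-to-treat is planned. Analysis as observed is a missing-data convention, so a failure who is assessed at 6 months counts. The flowchart and the timeline figure, which might show the path of trial failures, are not available here, and definitions of analysis sets commonly belong in an SAP.

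All of this stands, and it makes the biased comparison a risk rather than a stated rule. It does not remove the point. The start remains undefined for SCS, and the IPG reading is open because the 1-month visit pairs the start of BMT with implantation and subthreshold programming is done on implantation day. The attrition allowance is stated in this document. Continued follow-up is a protocol matter, because no SAP can recover 6-month data that were never collected.

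It is also fair to object that the 4–6 points depend on a cited source that is not at hand. That figure is conditional and is given as such.

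**Conclusion.** The point holds in this form: the sample size treats post-randomisation trial failures as attrition, which conflicts with the planned intention-to-treat analysis, and the visit timing and analysis rules leave room for those failures to fall out of the SCS arm only. If they do, the bias favours SCS. Multiple imputation, planned only as a sensitivity analysis, does not reliably correct it.

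The size is about 7 of 57 SCS patients. The overstatement is about 4–6 points on a 35.2-point difference if 47.8% refers to implanted patients and failures respond somewhere between never and the BMT rate. If 47.8% already covers failures, the rate stands and the error is a double count in the allowance. The sample size text needs correcting in either case.

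The issue is bias and a clear definition of what is compared. It is not power: with failures kept, the planned 114 still gives more than 80%. The gap between 57 per arm and the stated 80% power is a separate matter.

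**What to change.** 1. In section 20c, name intention-to-treat as the primary analysis and per-protocol as supportive.
2. State that every patient randomised to SCS, including trial failures, stays in follow-up to the 6-month assessment and is analysed in the SCS arm on observed status.
3. Time the assessments from a defined origin that exists for all randomised patients in both arms. Randomisation is one that qualifies.
4. Add a sensitivity analysis that counts trial failures without 6-month data as non-responders.
5. In Sample size {14}, remove the 12% attrition allowance and state whether 47.8% refers to implanted or to all trialled patients. If implanted, use the all-randomised rate (about 42–44% under the assumptions above).

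None of this alters the trial-success criteria or patient care. The cost is a short amendment, about 7 further sets of questionnaires and a slightly less favourable assumed SCS rate. If the start currently means implantation, an earlier common origin also brings the 6-month visit forward relative to the implant. No more patients are needed.
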